### Resource utilization and costs

The assessment of resource utilization and direct and indirect cost elements are included in the economic evaluation. Table 3 gives an overview of the different direct and indirect healthcare and non-healthcare cost items and includes information on the data sources for the valuation of utilization, unit prices and the corresponding perspective. The quantity of resources consumed by the participants and for the organization during the intervention will be derived from each trial site separately. Data on the use of health and social services during the entire study period will be collected using a RECETAS health economic questionnaire, registries, electronic medical records, and published literature. All items of the RECETAS health economic questionnaire are based on self-reported data or reported from the study nurse from the participants at t0, t1, t2, and t3. The RECETAS health economic questionnaire was developed based on published and unpublished literature [62–68]. Additionally, the questionnaire was discussed and adapted with each study site to ensure alignment with country-specific contexts and reflect the national healthcare setting, but it was not formally validated by participants or piloting. The questionnaire was part of the training of staff administering the questionnaires and is available from the authors upon request.

**Table 3 Tab3:** Overview of costs

Type of Cost	Resource and Cost Items	Specification/ Examples	Time Points	Perspective	Source of Resource Utilization	Potential Source of Unit Price
Direct Non-healthcare Costs	NBSP Preparation and Implementation Costs	Menu development, training facilitators, advertisement, insurance	t0, t1	Healthcare, Societal	Trial	Trial
	NBSP Intervention Trial Costs	Transportation, entrance fees, facilitators salary	t0, t1	Healthcare, Societal	Trial	Trial
Direct Healthcare Costs	Outpatient Hospital Services	General practitioner, specialist (e.g., psychiatrist, cardiologist), emergency care, nurse	t0, t1, t2, t3	Healthcare, Societal	Health economic questionnaire (self-reported), medical records	National physician fee schedules/ health services tariffs
	Inpatient Hospital Services	Emergency care physician (hospital), psychiatric center, general medical ward, general surgical ward, rehab clinic	t0, t1, t2, t3	Healthcare, Societal	Health economic questionnaire (self-reported), medical records	Hospital billing system, national Diagnosis Related Groups
	Health Care Professional (Home Visits)	General practitioner, nurse, physiotherapist	t0, t1, t2, t3	Healthcare, Societal	Health economic questionnaire (self-reported), medical records	Reimbursement rates from national physician fee schedules
	Primary Social Care	Home care worker, social worker, ambulance transport, community/ social services	t0, t1, t2, t3	Healthcare, Societal	Health economic questionnaire (self-reported), medical records	Health services tariffs
	Medication	Prescribed medication, non-prescribed medication	t0, t1, t2, t3	Healthcare, Societal	Health economic questionnaire (self-reported), medical records	National drug price database
Indirect Non-health care Costs	Time Costs	Informal/ Community care (e.g., relatives, neighbors), Participants	t0, t1, t2, t3	Societal	Trial	Average salary or minimum wage according to National Statistics
	Productivity Costs	Absenteeism (labor market earnings lost)	t0, t1, t2, t3	Societal	Trial	Average salary or minimum wage according to National Statistics

t0: baseline; t1: after 3 months; t2: after 6 months; t3: after 12 months

Direct costs related to the resource utilization of health care, such as medication, hospital stays, and physician visits, as well as the non-healthcare costs of the NBSP intervention will be included [69]. The NBSP preparation and implementation costs include, amongst others, the training and working time of the facilitators, the development of the NBSP menu and the advertisement and communication as part of the organization of the trial. Insurances specifically relating to the delivery of the NBSP intervention (e.g., insurance coverage in case of injury during group sessions or accidents occurring during activities in natural environments) will be included in the healthcare perspective as the insurance is paid by the healthcare payer and represents a direct cost of delivering the intervention. However, under the societal perspective, most of the insurance premiums are transfer costs in case of accident compensation with a negligible administrative cost ratio of typically less than 1%. Therefore, insurance premiums are not included in the societal perspective, as they represent mostly a redistribution of financial resources from the payer institution to the insurance provider [70, 71]. NBSP intervention trial costs include the transportation and the facilitators earnings, which will be calculated by multiplying hours worked by their average salary. The transportation costs of the facilitators and transportation to the intervention site will be considered. As the intervention primarily takes place in publicly accessible green or blue areas, although some nature-based activities are organized indoors, almost no venue costs are expected to arise. For the societal perspective, out-of-pocket costs for the usual care participants are collected regarding participation costs for comparable group activities in nature, such as equipment or transportation. Session-specific costs paid by the participants in the intervention group will also be considered (e.g., food and beverages).

The choice of the perspective of the economic evaluation is based on the study population and on national and methodological guidelines for economic evaluations of the trial sites [28, 72–74]. In Barcelona, the study population includes adults aged 18 years and older, and following the national recommendations a societal and a healthcare perspective is adopted [72]. For the societal perspective, indirect non-healthcare costs beyond the healthcare sector, such as time costs for community care and costs due to productivity losses will be assessed [69, 75]. The community care costs are based on informal care comprising the value of unpaid caregiver time or uncompensated household production. Costs due to productivity losses are related to the absenteeism of work or reduced productivity, such as labor market earnings lost or less earnings due to loneliness. The impact of valuing these productivity costs using the friction cost method will be explored [75, 76]. According to the friction cost approach, indirect costs due to productivity loss can be calculated by multiplying the incidence of unemployed participants with the minimum (or average) salary in Spain over the friction period, that is the average time to replace the employee (i.e., six weeks or end of the follow-up, whatever occurs earlier) [77, 78]. For the Czech Republic, the national guidelines recommend to adopt a healthcare perspective for economic evaluations [28, 73]. Although recommended generally in Finland [74], a societal perspective for costs will not be applied in the Helsinki trial because the target population are older people permanently residing in assisted living facilities and indirect costs referring to productivity losses and time costs are less relevant. Thus, the economic evaluation in Helsinki will be performed from a healthcare perspective.

In general, costs will be calculated by multiplying the amount of resources consumed by their corresponding country-specific prices. Costs of the NBSP intervention and control group will be accumulated over the time horizon of the trial and reported as total costs and as mean costs per participant in Euros (EUR) for Barcelona and Helsinki or Czech Koruna (CZK) for Prague. Costs for inpatient hospital services will be based on national Diagnosis Related Groups fees. Healthcare professionals and primary social care will be calculated by multiplying the number of contacts or hours of consultations with the national physician fee schedules or respective health services tariffs. Medication costs will be calculated by multiplying the dosage by the frequency and standard price over the one-year trial period. In addition, short-term temporary medications might be considered. Non-prescribed medications reflecting out-of-pocket payments for the participants will be considered only in the societal perspective. All costs will be adjusted to a standard reference year if necessary, using the consumer price index [79]. Due to the short time horizon of the trial, future costs and health outcomes are not discounted to present values [80, 81].

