### Interventions and comparators

In all three RCTs (Barcelona, Prague, and Helsinki), participants are randomized to an intervention or control arm. Detailed descriptions of both arms have been published previously [23, 30]. Briefly, in the intervention arm, participants participate in the “Friends in Nature” (FIN) intervention, an adaptation from the Circle of Friends^®^ methodology developed by the University of Helsinki [30], “customized to the specific target population in each trial and with a focus on nature-based activities” [23]. Two trained facilitators are assigned to each group to support the group dynamics by fostering empowerment and, at the end of the group process, independence from the facilitator. The training and mentoring process of the facilitators based on the Circle of Friends^®^ methodology has also been described previously [23, 30]. In the first session, an individualized one-to-one interview with the facilitators is conducted in Barcelona and Prague. Individuals are then allocated to take part in a program of weekly nature-based group activities (5–12 people) for nine sessions [23]. The activities vary from week to week, and include a combination of strategies promoting empowerment, social connectiveness, and participation in nature-based activities. The group stays together, and they discuss and decide on the activities. During this time, the facilitators keep a diary, instruct the group, assure connectivity, and assist in ensuring compliance. The control group receives usual care (UC). In Barcelona and Prague, UC consist of an individual NBSP interview at which participants receive a menu of nearby nature-based community resources to utilize individually, without further support [23]. Potential uptake of nature-based activities following the interview will not be considered in our health economic evaluations. In Helsinki, control participants receive normal care, which includes socializing in their ward, occasional recreational activities and some outdoor activities. Importantly, they do not participate in any further organized activities and receive no support from the FIN group or the facilitators.

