### Uncertainty analyses

It is recommended that economic evaluations alongside the trial address uncertainty around the cost effectiveness [27]. For this purpose, scenario and sensitivity analyses will be performed. Scenario analysis will be performed to assess the robustness of the cost-utility, cost-effectiveness, and cost-capability results. Alternative cost assumptions, including scenarios where fixed costs to set-up the program are excluded and analyses without imputation will be conducted. For sensitivity analyses, the nonparametric bootstrap method will be used with 10,000 replications on the individual-level RECETAS data set [103]. The results of the sensitivity analyses will be presented as a scatter plot and 95% confidence ellipses on the cost-utility, cost-effectiveness, and cost-capability planes. The 95% CIs for bootstrap simulations will be determined using the percentile method [104]. Uncertainty related to further parameterized assumptions will be assessed via probabilistic sensitivity analyses.

Decisions on cost effectiveness often depend on willingness-to-pay (WTP) thresholds. The incremental ratios can be compared to the relevant WTP threshold for an additional effectiveness unit determined by the responsible decision-making authority. The intervention, that is NBSP, can be identified to be cost effective if the incremental ratio is below the specific WTP. However, only few countries have an explicit WTP threshold. For example, Schwarzer et al. describe WTP thresholds in ten countries and identified only the United Kingdom and Thailand as having an explicit WTP threshold value [105, 106]. For the Spanish National Health System, estimates of such WTP thresholds range between 21,000 Euro and 24,000 Euro [107] or 25,000 Euro and 60,000 Euro [108] per QALY gained for being cost effective. In Czech Republic, a WTP threshold of 1.2 million CZK/QALY (approx. 47,000 Euro/QALY) is recommended by the State Institute for Drug Control [73]. Finnish national guidelines do not report a WTP threshold [74].

No established WTP threshold currently exists for the outcome of our CEA expressed as changes in loneliness. Therefore, results will be presented without applying a predefined threshold and interpreted in terms of relative cost-effectiveness and uncertainty (e.g., using cost-effectiveness acceptability curves).

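### Menu development and trial-related advertising are classed as NBSP costs although controls share some of them; if charged to the NBSP arm alone, base-case incremental cost is overstated

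*Protocol article*

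**What the plan says.** All references are to the protocol article.

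- **Classification.** The text on direct costs in Resource utilization and costs says that healthcare costs "as well as the non-healthcare costs of the NBSP intervention will be included". It then describes a preparation and implementation category that covers facilitator training and working time and "the development of the NBSP menu and the advertisement and communication as part of the organization of the trial". Table 3 gives the examples for this category as "Menu development, training facilitators, advertisement, insurance" and assigns it to both the healthcare and the societal perspective. The table has no column for trial arm.
- **What controls receive.** Interventions and comparators says of the Barcelona and Prague sites: "UC consist of an individual NBSP interview at which participants receive a menu of nearby nature-based community resources to utilize individually, without further support". For the third site it says: "In Helsinki, control participants receive normal care, which includes socializing in their ward, occasional recreational activities and some outdoor activities".
- **Costing of both arms.** The same costs section says: "Costs of the NBSP intervention and control group will be accumulated over the time horizon of the trial". It gives no rule for dividing set-up items between the arms.
- **Incremental cost.** Table 4 defines it as the mean cost in the NBSP arm minus the mean cost in usual care, and uses this one difference for the ICUR, the ICER and the ICCR.
- **Scenario.** Uncertainty analyses plans "scenarios where fixed costs to set-up the program are excluded". Set-up costs are therefore part of the base case.

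**The concern.** A difference in mean costs should contain only what the programme adds. Two of the items listed may not meet that test.

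The first is the menu. At two of the three sites the comparator consists of an interview and a menu, so developing the menu is an input to usual care as well as to NBSP. The cost table has no usual-care entry for the interview or the menu. The only programme-type spending named for controls is their out-of-pocket cost of comparable activities, and that counts only in the societal perspective.

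The second is advertising and communication, which the text ties to organising the trial. Where this means recruitment, the money is spent before randomisation, brings in both arms, and would not be spent if the programme were delivered routinely.

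An analyst who follows the labels would book both items to the NBSP arm. Incremental cost would then depend partly on how the trial was publicised and on a resource that controls also used. The error would have one direction, against NBSP, and would reach the cost-utility, cost-effectiveness, cost-capability and responder results together.

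**Working it through.** The article states no menu cost, advertising cost, incremental cost or ratio, so there is no figure of the plan's own to reproduce. The check has two parts.

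**1. Classification against receipt**

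| Item | Classed as | Who uses it |
|---|---|---|
| Menu development, Barcelona and Prague | NBSP preparation and implementation | Controls explicitly (Interventions and comparators); the Abstract describes NBSP as also providing a selection of resources |
| Menu development, Helsinki | Same category, if any is incurred | No menu described for controls |
| Individual interview, Barcelona and Prague | No line in Table 3 | Both arms |
| Advertising that recruits for the trial | NBSP preparation and implementation | Both arms, before randomisation |
| Advertising that promotes the programme | NBSP preparation and implementation | NBSP: a genuine programme cost |
| Facilitator training | NBSP preparation and implementation | NBSP arm; controls have no facilitated group |

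Some items in one NBSP-labelled category are therefore shared, some are research-driven, and some belong properly to NBSP.

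**2. Effect on the increment**

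Let F be the shared or research-driven amount, n the number in the NBSP arm, and ΔE the effect gain.

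- Charged wholly to NBSP: Δcost rises by F/n, and the ratio rises by (F/n)/ΔE when ΔE is positive.
- Charged per head to both arms: each arm carries F/(2n) per participant, so Δcost changes by F/(2n) − F/(2n) = 0.
- Excluded as a research cost: Δcost changes by 0.

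Inputs: 316 per trial (Sample size and missing data). The allocation ratio is not given in this article; assuming 1:1, n = 316/2 = 158. F and ΔQALY are assumptions.

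| Assumed F (EUR) | F/158 (EUR per NBSP participant) | ΔQALY 0.01 | ΔQALY 0.02 | ΔQALY 0.05 |
|---|---|---|---|---|
| 5,000 | 31.6 | 3,165 | 1,582 | 633 |
| 10,000 | 63.3 | 6,329 | 3,165 | 1,266 |
| 20,000 | 126.6 | 12,658 | 6,329 | 2,532 |

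The last three columns are EUR per QALY added to the ICUR. For scale, the article cites a Spanish threshold range of EUR 21,000 to 24,000 per QALY. The middle case is 3,165/24,000 = 13% to 3,165/21,000 = 15% of it. The direction follows from the arithmetic. The size reflects only the assumed inputs. Prague will report in CZK, so the euro figures do not carry over to that site directly.

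**The case against.** The strongest reply is that no sentence charges these items to the NBSP arm alone. Costs of both arms are to be accumulated, Table 3 is silent on arm, and the article calls the control contact itself an NBSP interview, so the label need not mean the intervention arm. Allocation by arm could also be costing detail left to a fuller plan. The first part stands: sole charging is implied, not stated, and the bias is conditional on it. The second part is weaker, because the article does more than stay silent. It introduces the category as the cost of the intervention, puts trial-related advertising and the menu into it, and gives controls no corresponding line.

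A second reply is that the article uses the word trial loosely. Its heading for transport, entrance fees and facilitator salaries also contains that word, although these are delivery costs. The advertising may therefore be programme outreach that routine delivery would need. This stands as a real ambiguity, and only the recruitment part is open to objection.

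A third reply is that the scenario without fixed set-up costs already shows readers how much they matter. It helps with the total. It does not isolate the shared or research-driven items, and it leaves the base case as it is. A reader might infer that the scenario also drops facilitator training; the article does not say which items it removes. The planned cost scenarios are not described as exhaustive, so a narrower one could be added.

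**Conclusion.** The point holds in conditional form. The article places a cost shared with controls at two sites, and advertising tied to organising the trial, in a category introduced as the cost of the NBSP intervention, and the base case contains that category. If those items are charged to the NBSP arm, incremental cost is overstated and every ratio that uses it is biased against NBSP.

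A reader might go further and conclude that the base case is inflated at all three sites and that the right increment for these items is zero. The documents do not support that. Charging to NBSP alone is not stated. The menu argument covers Barcelona and Prague only. Advertising needed for routine delivery is a proper NBSP cost, and zero applies only to items that are shared equally per head or are purely research-driven.

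The size cannot be known from the article. EUR 63 per participant for each EUR 10,000 rests on an assumed amount and on 1:1 allocation of 316; any figure per QALY also rests on an assumed gain. The case for acting is the one-way direction of the possible error and the small effort of removing it.

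**What to change.** Add a few sentences to Resource utilization and costs, with a matching entry in Table 3:

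- Exclude trial-recruitment advertising and other research-driven costs from the base case. Keep only the advertising and communication that routine delivery of the programme would need.
- In Barcelona and Prague, charge menu development and the individual interview per head to each arm that receives them, so that usual care carries its own cost.
- Keep facilitator training in the NBSP base case.
- Retain the scenario without set-up costs and list the items it removes. If wanted, show the trial-driven costs in a separate scenario.

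The cost is minor: cost items already planned for collection are reclassified, and the control interview has to be costed. Splitting recruitment from programme advertising takes some judgement, so the rule used should be recorded before costs are compared by arm.

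### Table 3 and the text of the protocol article disagree on which perspectives carry insurance, non-prescribed medication and control-arm activity costs

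*Protocol article*

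**What the plan says.** All three items are in the current Methods text of the protocol article; the third is repeated in its Discussion.

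- **Insurance.** Under Resource utilization and costs, insurance tied to delivering the intervention "will be included in the healthcare perspective as the insurance is paid by the healthcare payer". The text then argues that premiums are mostly transfers from society's viewpoint and concludes: "Therefore, insurance premiums are not included in the societal perspective". Table 3 lists "Menu development, training facilitators, advertisement, insurance" in the preparation and implementation row, and the perspective cell of that row names both healthcare and societal.
- **Non-prescribed medication.** The same section says "Non-prescribed medications reflecting out-of-pocket payments for the participants will be considered only in the societal perspective". The medication row of Table 3 reads "Prescribed medication, non-prescribed medication", again with both perspectives named.
- **Control-arm nature activities.** Interventions and comparators says of the Barcelona and Prague controls: "Potential uptake of nature-based activities following the interview will not be considered in our health economic evaluations". The Discussion repeats this for the control group. Yet Resource utilization and costs, in setting out what the societal analysis needs, says: "out-of-pocket costs for the usual care participants are collected regarding participation costs for comparable group activities in nature, such as equipment or transportation". Its next sentence adds that session costs paid by intervention participants are to be counted as well.

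The same section sets the perspectives: societal and healthcare for Barcelona, healthcare for Prague and Helsinki.

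**The concern.** Table 3 is introduced as showing the perspective that applies to each cost item, so an analyst may reasonably build the cost totals from it. Doing so puts insurance into a societal total from which the text excludes it, and puts participants' own spending on medicines into healthcare totals from which the text excludes that too. No footnote limits either row, and no order of precedence between table and text is given.

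The control-arm item matters for a different reason. Outcomes are analysed by intention to treat, so control participants keep any benefit from nature activities they take up. If the cost of that uptake is dropped while intervention participants' session costs are kept, spending of the same kind is counted in one arm only.

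At stake is the numerator of every incremental ratio. It matters most for the primary cost-utility ratio, which is to be read against willingness-to-pay values where they exist.

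**Working it through.** The article gives no amount for any of the three items, so there is no figure to reproduce. The check compares the rules and then applies the article's own definition in Table 4: incremental cost = mean cost (NBSP) − mean cost (usual care).

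**Step 1: the rules side by side**

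| Item | Table 3 | Text | Analysis affected |
|---|---|---|---|
| Insurance | Healthcare and societal | Healthcare only | Barcelona societal |
| Non-prescribed medication | Healthcare and societal | Societal only | Healthcare, all three sites |
| Control-arm activity costs | No separate entry | Collected for societal (costs section); uptake not considered (Interventions and comparators, Discussion) | Barcelona societal |

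Table and text agree on insurance in the healthcare perspective and on non-prescribed medication in the societal perspective, so nothing changes there.

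**Step 2: effect on incremental cost**

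Let I = insurance per NBSP participant, U = mean out-of-pocket activity cost per usual-care participant, and dM = NBSP minus usual-care difference in mean non-prescribed medication cost. None of these is given. I and U cannot be negative; dM can have either sign.

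*Healthcare perspective, each site.* Let H be the increment without non-prescribed medication.
- Following the text: H
- Following Table 3: H + dM
- Gap: dM

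*Societal perspective, Barcelona.* Let B be the increment with neither insurance nor control-arm activity costs, but with the intervention arm's session costs.
- Insurance out, control costs in (costs section): B − U
- Insurance out, control costs out: B
- Insurance in, control costs in: B + I − U
- Insurance in (Table 3), control costs out (Interventions and comparators, Discussion): B + I
- Gap between the extremes: (B + I) − (B − U) = I + U

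The two societal conflicts therefore add in the same direction. Counting insurance and ignoring control-arm costs both make NBSP look dearer.

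**Step 3: illustration by assumption only**

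Shift in the cost-utility ratio = cost shift per participant ÷ QALY gain. Both inputs are assumed.

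| Cost shift (EUR) | QALY gain 0.01 | QALY gain 0.05 |
|---|---|---|
| 10 | 10/0.01 = 1,000 per QALY | 10/0.05 = 200 per QALY |
| 50 | 50/0.01 = 5,000 | 50/0.05 = 1,000 |
| 100 | 100/0.01 = 10,000 | 100/0.05 = 2,000 |

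For scale, the Spanish threshold estimates cited under Uncertainty analyses run from EUR 21,000 to EUR 60,000 per QALY. The table shows only how sensitive the ratio is to a given shift. It does not show that a shift of any of these sizes will occur.

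**The case against.** **Insurance and medication.** These can be read as labelling slips. Table 3 is an overview that assigns perspective by row, and the entries in question are specifications or examples within a row. The text gives item-specific rules, with a reasoned argument in the case of insurance, and a specific rule would normally govern a bundled label. That largely stands: the text shows the intended rule, and the remedy is to correct the table. It does not remove the contradiction. It is also fair that medication costs arise in both arms, so only their difference reaches the increment, and nothing in the article suggests that this difference is large.

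**Control-arm activities.** The sentence in Interventions and comparators follows a description of resources that controls use individually, whereas the costs section speaks of comparable group activities. The Discussion's repetition sits among remarks on a diluted effect. A coherent reading is that outcomes will not be adjusted for uptake while costs are still recorded. This is the strongest objection, and it makes the third conflict softer than the other two. But both uptake sentences refer to the health economic evaluations without limit. The costs section ties the collection to the societal perspective and then says the intervention arm's session costs are counted as well, which implies that the usual-care costs are counted.

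**Stronger readings that the article does not support.** A reader might infer an established bias against NBSP. The article supports only a conditional one: it arises if the uptake sentences are applied to costs, and then only in Barcelona's societal analysis. A reader might also infer that the interview and menu, which Barcelona and Prague controls also receive, are wrongly charged to NBSP alone. Nothing says so. Table 3 lists menu development as a preparation cost without allocating it to an arm, and the text accumulates costs for both arms.

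**Conclusion.** The concern holds as a conflict between rules in the current text. The insurance and non-prescribed medication contradictions are plain. The control-arm item is an ambiguity that has a directional consequence under one of its readings: incremental cost in Barcelona's societal analysis is overstated by U, the mean control-arm activity spending.

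The reach is limited. The Prague and Helsinki evaluations are affected only by dM, Barcelona's healthcare analysis likewise, and Barcelona's societal analysis by at most I + U. The size of each is unknown, and the illustration rests wholly on assumed cost shifts and QALY gains. This should be corrected because the article presents itself as a prospective, reproducible framework and the correction is cheap. It does not undermine the design.

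**What to change.** 1. In Table 3, give insurance its own row marked healthcare only, and non-prescribed medication its own row marked societal only, so that both match the text.
2. In Interventions and comparators and in the Discussion, limit the uptake sentences to effects: outcomes will not be adjusted for control-arm uptake of nature activities.
3. In Resource utilization and costs, state that the out-of-pocket activity costs collected from usual-care participants enter Barcelona's societal analysis on the same basis as the intervention arm's session costs.

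The cost is a table edit and a few sentences. The article says the control-arm out-of-pocket costs are collected, so no new data are needed. The edits are best made before cost results by arm are seen.

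### The exploratory friction-cost formula for Barcelona counts only job loss, so absence from work among participants who keep their job is costed at zero

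*Protocol article*

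**What the plan says.** All the relevant text is in the Methods section of the protocol article, under Resource utilization and costs.

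- **Cost item.** Table 3 lists productivity costs as "Absenteeism (labor market earnings lost"), collected in the trial at t0, t1, t2 and t3 for the societal perspective. The unit price is "Average salary or minimum wage according to National Statistics".
- **Definition.** "Costs due to productivity losses are related to the absenteeism of work or reduced productivity, such as labor market earnings lost or less earnings".
- **Alternative valuation.** "The impact of valuing these productivity costs using the friction cost method will be explored".
- **Formula.** The next sentence gives the calculation: "indirect costs due to productivity loss can be calculated by multiplying the incidence of unemployed participants with the minimum (or average) salary in Spain". That salary is applied for the length of the friction period, which is explained as the average time needed to fill the post and set at "six weeks or end of the follow-up, whatever occurs earlier".

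Only Barcelona has a societal perspective. Prague and Helsinki use a healthcare perspective, in which productivity costs do not enter.

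**The concern.** The word *these* in the sentence announcing the friction method ties it to the costs just defined: absence and reduced productivity. The formula has no term for either. Its quantity is the number of participants who become unemployed, and nothing elsewhere in the article adds a term for absence.

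The stated aim is to see what difference the friction method makes. That requires the same quantity of lost work to be valued in two ways, with and without a cap at the friction period. If the quantity changes as well, a difference between the two results cannot be attributed to the method. A reader of the results would probably attribute it to the method all the same.

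**Working it through.** The article states no productivity cost, so there is no figure to reproduce. The check applies the formula as printed and compares it with absence time capped at the same friction period. The unit is one day's wage, so no salary has to be assumed.

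**Inputs from the article:** friction period of six weeks; quantity in the formula, participants becoming unemployed; quantity in the definition and Table 3, absence.

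**Assumptions:** a five-day week, so the friction period is 6 × 5 = 30 working days, with at least six weeks of follow-up remaining. Rates of absence and job loss are illustrative; the article gives none.

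**Step 1: one employed participant with one absence spell who keeps the job**

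| Days absent | Full valuation | Capped: min(days, 30) | Formula as printed |
|---|---|---|---|
| 5 | 5 | 5 | 0 |
| 10 | 10 | 10 | 0 |
| 20 | 20 | 20 | 0 |
| 30 | 30 | 30 | 0 |
| 60 | 60 | 30 | 0 |

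The genuine effect of the friction method is the step from the second column to the third. It is nil up to 30 days and appears only in the 60-day row. The fall to zero in the last column comes from the choice of quantity, not from the cap. The formula does cost a job loss at least six weeks before the end of follow-up: 30 day-wages.

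**Step 2: mean per participant**

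With job-loss incidence u, the formula gives 30u. With a share a absent for d days each (d at most 30), the omitted absence is a × d. The omitted share of the combined loss is a × d / (30u + a × d).

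| u | Formula, 30u | a × d = 0.2 × 10 = 2 | a × d = 0.4 × 10 = 4 | a × d = 0.4 × 20 = 8 |
|---|---|---|---|---|
| 1% | 0.3 | 87% | 93% | 96% |
| 3% | 0.9 | 69% | 82% | 90% |
| 5% | 1.5 | 57% | 73% | 84% |

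The range is 57% (2 / 3.5) to 96% (8 / 8.3). It falls if absence is rarer: one day in 50% of participants gives 0.5 day-wages, and with 3% job loss the omitted share is 0.5 / (0.9 + 0.5) = 36%.

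**Step 3: what a between-arm comparison could miss**

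Suppose job loss is 3% in both arms, and 40% of participants are absent for 6 days with the intervention and 10 days with usual care. The formula gives 0.03 × 30 − 0.03 × 30 = 0. Capped absence gives 0.4 × 6 − 0.4 × 10 = −1.6 day-wages per participant. This shows the mechanism; the difference between arms is assumed.

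**The case against.** The strongest reply is that the reach is small. The friction valuation is something to be explored, at one site, under one of that site's two perspectives. Table 3 still lists absenteeism priced at a wage, and the general costing rule in the same section is resources multiplied by price. The formula also captures one real part of lost earnings, namely job loss. All of this stands and limits the point to the exploratory analysis.

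A reader might infer more, in four ways that the article does not support:

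- **That absenteeism drops out of the base case.** The formula belongs to the alternative valuation, and Table 3 keeps absenteeism as a cost item.
- **That participants already unemployed at baseline are charged six weeks' salary.** The article speaks of incidence, which means new cases, and ties the friction period to replacing an employee. Someone without a job at baseline has no post to be refilled, so a cost built on baseline unemployment has no basis in the text.
- **That unemployment unrelated to the intervention distorts the result.** The evaluation compares randomised arms by intention to treat. Unrelated events can occur in both arms, and the same is true of unrelated sick leave.
- **That the societal cost-utility ratio is shown to move.** The ratio depends on the difference between arms, and the article gives no data on that difference.

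Nor can the gap be put down to condensation in a journal article. The article prints a formula, and that formula conflicts with the definition just before it and with Table 3.

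**Conclusion.** The formula is wrong as written for the stated purpose. In the exploratory friction-cost valuation for Barcelona, it values job loss only and assigns zero to absence and reduced productivity among those who stay in work. The comparison with the absenteeism-based valuation then mixes a change of quantity with a change of method.

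That conclusion follows from the text and needs no assumption. The size does: 57–96% of the combined loss is omitted under the illustrative ranges above, and 36% in the low-absence example. No effect on the primary analysis at any site, or on the base-case absenteeism costing, is established.

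**What to change.** Replace the formula sentence with one that keeps the quantity fixed:

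- Value the absence time of employed participants (and reduced productivity, if it was measured) from the data already planned at t0 to t3, at the same wage as in the absenteeism-based valuation, capped at the stated friction period of six weeks or the end of follow-up.
- Apply the cap per absence spell if spells were recorded, and otherwise per recall period. The article does not show which is possible, because the questionnaire is available only on request.
- Add job loss occurring after randomisation as a separate component under the same cap.

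The two valuations of absence then differ only through the cap, and the job-loss component can be reported separately.

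The cost is a sentence or two of text and a short change to the analysis code. Barcelona recruitment finished in May 2024, so the rule should be written around the absence data actually collected. The per-recall-period option avoids any need for spell-level records.
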